## *Recruitment and Screening Procedures*

The recruitment of 1300 participants will occur through six sites:

- Random sample of 1000 Latinx immigrant adults in New Mexico recruited by LD Insights/Latino Decisions
- 60 Latinx immigrant adults utilizing services at Centro Sávila
- 60 Latinx immigrant adults utilizing services at Encuentro
- 60 Latinx immigrant adults connected with New Mexico Dream Team
- 60 Latinx immigrant adults utilizing services at New Mexico Immigrant Law Center
- 60 African refugee adults connected with United Voices for Newcomer Rights

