The other 240 Latinx immigrant adults and the 60 African refugee adults will be recruited by CBO partners, all of whom have partnered with UNM on studies of the Refugee and Immigrant Well-being Projects and have successful histories of recruiting study participants. The staff of each CBO speak the languages of participants they will recruit (Spanish, Swahili, Kirundi, Kinyarwanda). As evident from the numbers of clients or participants engaged with each CBO per year (see Table 2), we anticipate that the recruitment goal of 60 adult participants aged 18 or older per site is very feasible. With support from the Research Coordinator [name], Community-Based Research Specialist [name], and graduate student [name], each site will share information about the study through their different activities (see Intervention Recruitment Flyer), including classes, groups, individual services, and community meetings (all of which are remote/virtual right now due to COVID-19). CBO staff will ask interested people if a study team member can call them to explain the study in more detail. During phone calls with potential participants (in their preferred language, see Intervention Recruitment Script), eligibility will be verified, the study will be explained (including random assignment to RIWP intervention or services-as-usual control group), and consent will be obtained (or reviewed for participants to consider). Participants will have the option to complete consent and the survey interview at the time of the phone call or to schedule another meeting via phone or Zoom to complete consent and the survey interview.

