Random assignment. Randomization of the CBO-recruited sample (n=300) into RIWP or treatment-as-usual waitlist control group (TAU) will occur after completion of timepoint 1 surveys and will be based upon a computerized algorithm that stratifies randomization by CBO site.

RIWP implementation. RIWP will be implemented with 30 participants from each CBO site (n=150) from Months 5-12. RIWP will be integrated into existing activities and services in different ways at each site, with the goal of creating a sustainable intervention and multilevel change. All RWIP activities (Learning Circles and advocacy) will be conducted remotely for now. Once state and UNM COVID restrictions are lifted, some in-person Learning Circles and advocacy meetings may occur. The treatment-as-usual waitlist control group will participate in RIWP after two years (3 timepoints) of data collection, from Months 29-35. RIWP involves a sustainable and replicable partnership model between refugees, CBOs, and universities (see Figure 1 for conceptual model). Newcomer families and undergraduate advocates work together for 16 weeks to: a) increase newcomers’ abilities to navigate their new communities; b) improve newcomers' access to community resources; c) enhance meaningful social roles by valuing newcomers' cultures, experiences, and knowledge; d) reduce newcomers' social isolation; and e) increase community responsiveness to newcomers. RIWP is implemented by university students enrolled in a 2-semester course, and has two elements: 1) Learning Circles, which involve cultural exchange and one-on-one learning opportunities; and 2) Advocacy, which involve collaborative efforts to mobilize community resources related to health, housing, employment, education, and legal issues and to create policy/system changes. Meeting in weekly Learning Circles, newcomers and their student partners learn from each other during cultural exchange time designed to facilitate sharing of cultural and intergenerational knowledge and to help newcomers recognize their contributions and potential to effect changes in their communities. During one-on-one learning time, newcomer and student participants practice English, fill out job applications, and engage in other activities newcomers want to pursue to expand knowledge, improve skills, or accomplish goals. RIWP is holistic, multilevel, and strengths-based, and has an explicit social justice orientation that is informed by an ecological perspective. A holistic intervention is essential because it addresses the multiple sources of newcomers’ psychological distress, including psychological (past traumas), material (poverty, lack of access to resources), physical (physical ailments from war, violence and deprivation), social (loss of meaningful social roles and social support), educational (limited English proficiency, literacy), and cultural disconnection from traditional cultural practices). A strengths-based perspective is important because newcomers have survived in the face of tremendous hardships and have numerous strengths on which to build, including cultural knowledge (and often extensive cross-cultural experience), resourcefulness (experience operating in resource scarce situations), effective coping strategies (that have enabled them to survive), multilingual abilities (many arrive already speaking two or more languages), and often strong family and community bonds and support. Newcomers are often pathologized by well-intentioned service providers and systems, rather than recognizing that most are resilient people who have faced abnormally difficult circumstances. Not only is it crucial for newcomers’ mental health and well-being to acknowledge their expertise and build upon their strengths, but also their knowledge and experiences are assets from which other Americans can benefit. Thus, mutual learning is an intentional and core component of RIWP. This emphasis also ensures that RIWP is appropriate for multiple linguistic and cultural groups who can participate simultaneously and learn from one another as well as from longer-term residents of the U.S. Guided by ecological theory, RIWP focuses not only on newcomers adjusting to their new contexts, but also on changing environments when they are inequitable or constraining (e.g., mobilization or redistribution of resources). Ensuring that RIWP creates change at multiple levels is important because newcomers have urgent learning, resource, and health needs that must be addressed at the individual level in order to enable them to work collectively with others to create community and structural changes that address the root causes of mental health disparities and social inequities, which result in sustainable social change.

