**Aim 1.** Test the effects of the RIWP intervention to reduce adverse consequences of the COVID-19 pandemic. The principal objective of this study is to test the efficacy of the RIWP intervention for participants recruited from CBOs. Because only individuals recruited from the CBO sample are eligible to be randomized to receive the RIWP intervention or treatment as usual, analysis for this aim includes only CBO participants. To examine the effects of the RIWP intervention, we propose a linear model with random effects for individuals. As randomization happens within CBO, there is not an explicit random effect for this included, but we do propose to use sandwich estimators,^99,100^ to adjust standard errors for any unexpected impacts of this clustering. In mixed notation the model for psychological distress is:

${Distress}_{ti}= B_{00}+{B_{01}\left( RIWP \right){+B}_{02}\left( Time \right){+B}_{03}\left( Time*RIWP \right){+\boldsymbol{B}}_{\mathbf{0}\boldsymbol{N}}\left( \boldsymbol{covariates} \right)+ r_{0ij}+r_{2ij}(Time)+ e}_{ij}$

where participation in the RIWP plus CBO is indicated by a dummy code for RIWP. Because baseline data is collected before randomization, time is centered at baseline and our aim is answered by B_03_ which is the difference in slopes of levels of distress, adjusted for covariates, between those who experience RWIP+CBO intervention and those in the CBO group.

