**Secondary Aims.** (a)   Examine mechanisms of intervention effectiveness. This secondary aim will be examined through structural equation modeling (SEM) to provide tests of mediation effects through which outcomes are impacted by hypothesized mechanisms. The same models for changes in outcomes which are developed on the random sample^110^ will be used in these analyses. These analyses assess whether differences in outcomes between treatment groups are due to changes observed in protective factors from baseline to post-intervention.^111^ Significant indirect effects are anticipated linking the RIWP intervention with lower follow-up levels of distress, stressors, and economic precarity, via pre-to post-intervention increases in protective factors. Bootstrapped standard errors^105^ will be used to derive confidence intervals for these mediated effects; standard errors will be adjusted for clustering of participants within CBOs using sandwich estimators.^106^ (b) Explore whether race/ ethnicity, biological sex, gender identity, sexual orientation, age, and SES moderate intervention impact. For this secondary aim, stratification variables will be incorporated as level 2 covariates in the models described above. Moderation will be assessed via interactions between the multiple levels of treatment and each of these moderators.^107^ (c) Track local/state policy changes to obtain preliminary estimates of effects of these structural interventions on mental health, stressors, and economic precarity using propensity score matching. This aim will evaluate the impact of receiving the structural interventions which are the outcome of Aim 3 on mental health, stressors, and economic precarity. We propose to use propensity scores, but in this case where the treatment is receiving a structural intervention. Propensity scores will be developed using baseline data to predict the probability of receiving a structural intervention. We will then assess the impact of these interventions using matched samples in random effects models. Mediation will be examined using Sobel’s test to examine whether RIWP effectiveness had an indirect effect on mental health, stressors, and economic precarity through structural interventions (local/state policy changes).^108–110^ This is a secondary aim because, while important, there is not enough information to assess power a priori.

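### If secondary aim (b) inherits Aim 1's CBO-clustered sandwich errors, the race/ethnicity-by-RIWP test rests on one cluster, and its standard error is about 36% of the correct size

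*Protocol*

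**What the plan says.** All references are to the Protocol.

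- **Secondary Aims (b)** (Data Analysis/Statistical Considerations) sets out to "Explore whether race/ ethnicity, biological sex, gender identity, sexual orientation, age, and SES moderate intervention impact". The moderators enter the models already given for the main aims as person-level covariates and are tested by interaction with the levels of treatment. The paragraph names no variance estimator.
- **Aim 1** (same section) has random effects for individuals and none for CBO. It adds sandwich estimators "to adjust standard errors for any unexpected impacts of this clustering". In context the clustering is by CBO, and secondary aim (a) says so explicitly for its own sandwich errors.
- **Aim 2** (same section) has CBO and RIWP terms in one equation, with random effects for CBO and no sandwich.
- **Recruitment and Screening Procedures** lists "60 African refugee adults connected with United Voices for Newcomer Rights" and four other CBOs with 60 Latinx adults each. The comparison group is the "Random sample of 1000 Latinx immigrant adults in New Mexico recruited by LD Insights/Latino Decisions".
- **Random assignment** "stratifies randomization by CBO site". The paragraph on RIWP implementation puts 30 participants per site in RIWP and says that "RIWP will be integrated into existing activities and services in different ways at each site".

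**The concern.** Within the randomized sample, African refugee status and membership of one CBO are the same variable. A sandwich estimator clustered on CBO learns the variance from how cluster scores scatter around zero. A term that lives entirely inside one cluster gives it nothing to learn from: fitting the term forces that cluster's score to zero. The reported error then reflects only the spread among the four Latinx sites and omits the sampling error of the 60 African participants.

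At stake is a named secondary question: whether RIWP works differently for African refugees and Latinx immigrants. A significant result could come from an error bar that is far too short. Even with a correct error bar, it could be read as an ethnicity effect when it is equally a site effect.

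**Working it through.** **Inputs from the Protocol.** Five sites of 60, 30 per arm; 10% attrition in the CBO sample, so 27 per arm per site; baseline-to-posttest correlation .68; ICC .03; effect size .30. Two-sided α = .05 is assumed, because the Protocol states none.

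**Reproducing the plan's figure.** The residual SD after baseline adjustment is √(1 − .68²) = .733. With 135 per arm the SE of the RIWP effect is .733 × √(2/135) = .0892. Then .30/.0892 = 3.36, and Φ(3.36 − 1.96) = .92, against the stated Aim 1 power of .91. The inputs are therefore the right ones.

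**Why the African site drops out.** The columns for African status and its interactions with RIWP and time are non-zero only for that site. The estimating equations set their total score to zero, so that site's score on those terms is zero. In simulation the largest value was 3e-13.

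**Size of the error.** Let s² be the variance of one site's estimated RIWP effect: s² = .5376 × 2/27 = .0398.

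- The contrast is the African site's effect minus the mean of four Latinx site effects. Its true variance is s²(1 + 1/4) = .0498, so the true SE is .223.
- The sandwich gives 0 for the African part and Σ(d_j − mean)²/16 for the Latinx part, with expectation (3/16)s².
- The test statistic is therefore √(1.25/(3/16)) = 2.58 times a t variable on 3 df. With a normal reference, P(|t₃| > 1.96/2.58) = .503.
- With a G/(G−1) = 1.25 factor the multiplier is √(16/3) = 2.31, giving .458 (normal) or .316 (t on 4 df, cut-off 2.776).

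**Rejection rate with no moderation, nominal 5%**

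| Variance and reference | Formula | ANCOVA simulation (4,000 trials) | Five-wave mixed-model simulation (700 trials) |
|---|---|---|---|
| Plain sandwich, normal | 50.3% | 50.5% | 50.4% |
| G/(G−1) factor, normal | 45.8% | 45.9% | 46.9% |
| Plain sandwich, t(4) | 36.1% | not run | 37.7% |
| G/(G−1) factor, t(4) | 31.6% | 31.8% | 32.3% |
| Model-based SE | not derived | 5.1% | 5.1% |

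The mean sandwich SE was .080 against a true .223 in the ANCOVA runs (.080/.223 = 36%), and .031 against .088 in the mixed-model runs (35%).

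**Is this just the usual five-cluster problem?** Only in part. In the same mixed-model simulation, a moderator that varies within sites (sex) rejected 17.6% with the plain sandwich and normal reference. Most of the excess for race/ethnicity comes from its coinciding with site.

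**Limit of model-based errors.** Suppose the RIWP effect varies between sites with SD τ (assumed; the Protocol gives none). The true variance becomes 1.25(s² + τ²), while the model-based SE still uses 1.25s². The effective cut-off is 1.96 × √(s²/(s² + τ²)):

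- τ = .15: 1.96 × √(.0398/.0623) = 1.57, rejection about 12% (simulated 11.4%).
- τ = .20: 1.96 × √(.0398/.0798) = 1.38, rejection about 17% (simulated 16.3%).

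In the five-wave simulation, an assumed site SD of 0.1 in the treatment slope gave 21.7%.

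**The case against.** A reader might infer that the Protocol prescribes a test that is a coin flip. The text does not go that far, for three reasons.

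- Aim (b) does not name the sandwich, although aim (a) in the same paragraph does. Aim (b) also speaks of several levels of treatment, and the Aim 2 model holds both levels with CBO random effects and no sandwich. Because RIWP is randomized within CBO, CBO effects largely cancel from the RIWP contrast. A pre/post check with a CBO random intercept (500 replicates, ICC .03, many convergence warnings, so approximate) rejected 5.4%.
- A rate near one half needs a normal reference. The Protocol fixes no reference distribution or small-sample correction, and a statistical analysis plan may do so. The corrected t(4) version still rejects about 32%.
- The zero-variance result assumes race/ethnicity is coded African refugee versus Latinx. The target-population section describes two racial/ethnic groups, which supports that coding, but race/ethnicity is also a survey item and no coding is fixed.

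These points make the finding conditional but do not remove it. Aim 1 is where the Protocol models the randomized RIWP comparison, and nothing in aim (b) replaces its variance method. The longitudinal form is provisional, but the zero score does not depend on it: two-wave and five-wave versions behaved alike.

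The objection that the aim is exploratory is fair and limits severity. No primary aim depends on this term. The aim is nevertheless named and given a power of .87.

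A second tempting inference is that model-based errors make this a valid ethnicity test. They do not: with one African site, no variance estimator can separate ethnicity from site.

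**Conclusion.** The point holds conditionally. If aim (b) uses the Aim 1 model with CBO-clustered sandwich errors and codes race/ethnicity as African refugee versus Latinx, the SE of the moderation term is about 36% of its correct size. With no moderation, the test rejects about 46-50% of the time with a normal reference and about 32% with a G/(G−1) factor and t(4). If the Aim 2-type model with CBO random effects and model-based errors is used, this failure does not arise.

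Under either model the contrast is one site against four. Read as an ethnicity test, it rejects about 11-16% at an assumed site-to-site SD of .15-.20 even with model-based errors. At the CBO-versus-random-sample level, an African-versus-Latinx interaction cannot be estimated, because the random sample is Latinx only.

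This should be corrected before analysis. It concerns one exploratory secondary term, not the main Aim 1 test.

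**What to change.** In Secondary Aims (b), add wording to this effect:

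- The race/ethnicity-by-RIWP term, coded African refugee versus Latinx, is tested with model-based standard errors, participants being the units randomized within CBO. The CBO-clustered sandwich is not used for it.
- The result is reported as the African refugee site versus the four Latinx sites. The report states that ethnicity cannot be separated from site and that the SE does not cover site-to-site variation in the RIWP effect.
- An African-versus-Latinx interaction with CBO-versus-random-sample is not estimated, because the random sample contains no African refugees.

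Simple re-randomization within CBO is not a substitute: it tests the null of no RIWP effect rather than of equal effects.

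The cost is a few sentences, with no change to recruitment, randomization or data collection. The SE becomes nearly three times as large (.223/.080 = 2.8) and the interpretation narrower. With that SE, power for an interaction of .30 is about Φ(.30/.223 − 1.96) = 27%, so a null result would say little.

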
# OBJECTIVES/AIMS

The goal of this research is to advance the science of multilevel mental health interventions that aim to reduce the disparate, adverse mental health, behavioral, and socioeconomic consequences of the COVID-19 pandemic that are a result of complex interactions between underlying structural inequities and numerous barriers to health care. This community-based participatory research study builds on a long-standing collaboration with 5 community-based organizations (CBOs) and employs a longitudinal waitlist control group design with 5 time points over 32 months. A random probability sample of 1000 Latinx immigrants (RS) will be compared with 240 Latinx immigrants and 60 African refugees recruited through CBOs and randomly assigned to an efficacious peer advocacy and learning model (RIWP; n=150) or a treatment-as-usual waitlist control group (TAU; n=150). This innovative design allows for testing of three nested levels of intervention: 1) peer intervention model; 2) engagement with CBOs; and 3) structural interventions expected in response to the pandemic (e.g., state relief for mixed status families and expanded health insurance coverage), to which all 1300 participants would potentially be exposed. We propose three primary aims to advance mental health intervention and disparities research:

**Aim 1.** Test the effects of the RIWP intervention to reduce adverse consequences of the COVID-19 pandemic for Latinx and Black immigrants and refugees.

**1.1** *Primary Outcomes:* RIWP participants will have decreased psychological distress, daily stressors, and economic precarity as compared to randomly assigned treatment-as-usual waitlist control group (TAU).

**1.2** *Secondary Outcomes:* RIWP participants will have increased protective factors (social support, access to resources, English proficiency, cultural connectedness, health services use).

**Aim 2.** Test the effects of engagement with CBOs to reduce adverse consequences of the COVID-19 pandemic for Latinx and Black immigrants and refugees.

**2.1** *Primary Outcomes:* CBO participants will have decreased psychological distress, daily stressors, and economic precarity as compared to the comparison group of randomly sampled immigrants (RS).

**2.2** *Secondary Outcomes:* CBO participants will have increased protective factors (social support, access to resources, English proficiency, cultural connectedness, health services use).

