This study is specifically designed to be sensitive to the changing impacts of the pandemic and the effectiveness of the multilevel interventions in reducing those. Thus, we propose 5 data collection points, every 8 months over 32 months. Our primary outcomes – psychological distress, daily stressors, and economic precarity – tend to be moderately stable^93–98^ but may also be impacted by shocks such as losing a job or getting COVID-19. Given the unknown trajectory of the pandemic and the path of economic recovery, we do not know a priori what the best approach to use for the longitudinal data will be. Therefore, our proposal is to use those in the random comparison sample in order to explore longitudinal models which will capture a large portion of the variability in outcomes over time while also maximizing power to find treatment effects. For example, modeling effects on mean levels of the outcomes post baseline would involve only 1 model parameter but would miss much of the nuance in the data. The comparison respondents will allow us to examine possible alternatives (linear change, piecewise change, adjustments for time-varying events including unemployment and COVID infections) in data without treatment effects. We will conduct analyses and publish a paper which examines fit of alternative longitudinal models to the data, and we will conduct additional power analyses before choosing the approach which best balances model fit and power. For the remainder of the data analysis section, we assume a relatively simple model with an intercept and linear change, while power analyses assume a simple pre-post design which will result in conservative estimates of power.

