**Aim 3.** Test the effects of RIWP and engagement with CBOs to increase access to benefits of structural interventions (local/state relief-related policies). For this aim, the outcome will be a binary indicator for whether each participant accessed the structural interventions which are implemented. The analyses will be similar to Aim 2, but will use a logit link and consequently drop the e_tij_ term. As mentioned above, while this is written to assume linear changes, we have proposed a process for selecting the longitudinal model to be used with data from the comparison sample and using statistical simulations to evaluate power of the different alternatives.

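### Secondary aim c matches on baseline data only, although relief can be received at any point over 32 months and later shocks that move the outcomes plausibly also drive receipt

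*Protocol*

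**What the plan says.** Under Secondary Aims (c) in Data Analysis/Statistical Considerations, the exposure is receipt of relief: "We propose to use propensity scores, but in this case where the treatment is receiving a structural intervention". The time point of the covariates is fixed: "Propensity scores will be developed using baseline data to predict the probability of receiving a structural intervention". The outcome step follows: "We will then assess the impact of these interventions using matched samples in random effects models".

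The receipt variable is the Aim 3 outcome, worded per participant: "the outcome will be a binary indicator for whether each participant accessed the structural interventions which are implemented". Its model, however, is longitudinal: "The analyses will be similar to Aim 2, but will use a logit link and consequently drop the e_tij_ term".

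Two statements elsewhere bear on timing and confounding. OBJECTIVES/AIMS describes the policies as "structural interventions expected in response to the pandemic", so they lay ahead when the study was designed, and follow-up is long: "we propose 5 data collection points, every 8 months over 32 months". On the primary outcomes, the protocol says that they "may also be impacted by shocks such as losing a job or getting COVID-19".

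**The concern.** Baseline matching suits an exposure that is already in place at baseline. That is roughly the situation in Aim 2, where the protocol notes that contact with the community organizations predates the study. Aim c carries the same recipe over to an exposure that starts later.

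Someone who loses a job after T1 is likely to report more distress and more economic precarity, and is also plausibly more likely to seek relief. The second link is an inference; the first is the protocol's own statement. A score built from T1 data treats this person as equal to a matched person who kept the job, so recipients look worse for reasons unrelated to relief. This holds however receipt is coded.

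The coding raises a further, conditional problem. If each person carries one ever-received label, survey waves before receipt enter as treated waves and dilute the contrast.

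Structural intervention is one of the three levels that the design sets out to test, and aim c is where its effect on mental health is estimated. A bias toward no benefit or harm could mislead readers about relief policy.

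**Working it through.** **The plan's own figure.** The Power paragraph gives .80 at d = .23 for aim c. Group sizes and alpha are not stated. With two-sided alpha .05 (assumed), power = Φ(d·√(n/2)/SD − 1.96):
- 160 treated matched 1:1, SD = √(1 − .68²) = .733: .23 × √80 / .733 = 2.81, power .801.
- 300 treated matched 1:1, SD = 1: .23 × √150 = 2.82, power .804.

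The figure is attainable but cannot be tied to one design. It does not decide the point.

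**Step 1. Dilution, only if an ever-received label is used.** Take the four post-baseline waves T2 to T5 and a true effect of 0.23. The contrast shrinks by the share of recipients' waves that come after receipt. The timing of receipt is assumed.

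| Timing of receipt | Share of T2–T5 after receipt | Effect seen |
|---|---|---|
| All by T2 | 1.00 | 0.23 |
| Even over four intervals | (4+3+2+1)/16 = .625 | 0.14 |
| All in the last interval | .25 | 0.06 |

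**Step 2. Confounding by later shocks, under either coding.** Five waves were simulated for 200,000 people. From the protocol: correlation .68 and true effect -0.23 (the d of .23, signed as a fall in distress). Assumed: a lasting shock with 10% probability per interval, which worsens distress and raises the log-odds of receipt; ever-receipt then lies between 17% and 29%. Adjustment for the baseline outcome stands in for the baseline score.

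| Shock effect (SD) | Log-odds of receipt | True effect | Ever-received label | Receipt by wave | By wave, shock adjusted |
|---|---|---|---|---|---|
| 0 | 0 | -0.23 | -0.15 | -0.23 | -0.23 |
| 0.3 | 1 | -0.23 | -0.09 | -0.18 | -0.23 |
| 0.5 | 1 | -0.23 | -0.06 | -0.14 | -0.23 |
| 0.5 | 2 | -0.23 | +0.03 | -0.04 | -0.23 |
| 0.5 | 1 | 0 | +0.08 | +0.09 | 0.00 |

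The first row isolates the dilution of Step 1: coding by wave removes it. The other rows show that coding by wave does not remove confounding by shocks; adjustment for the shock does.

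**Step 3. Does a lagged score suffice?** In a second simulation (assumed 12% per interval, 0.4 SD, odds ratio 3; true -0.23), the ever-received label gave -0.02 to -0.07, and receipt by wave with baseline adjustment gave -0.13 to -0.18. Matching on the preceding wave among people not yet receiving relief gave about -0.18. Adding shocks from the same interval restored -0.23. With waves 8 months apart, a job loss and the relief that follows it can fall between the same two surveys, which is why the lagged score alone falls short.

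**The case against.** **The ever-received rule is not written.** A reader might infer that the protocol defines treatment as receipt at any time in follow-up and counts earlier waves as treated. It does not say so. The Aim 3 model keeps the time terms of Aim 2, which fits receipt recorded by wave, and a statistical analysis plan could settle the coding. This stands, so the dilution is conditional. It does not touch the baseline-only score, which is a stated rule.

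**Time-varying adjustment is foreseen.** The paragraph on longitudinal models lists adjustment for unemployment and COVID infection, and Step 2 recovers the true effect once the shock is adjusted for. But this is one candidate, to be chosen in the comparison sample, and aim c is not committed to it. If relief itself changes employment, adjusting for employment measured at the same wave could also remove part of the relief effect.

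**Power.** A reader might infer that power drops from .80 to .42, from a noncentrality of 2.80 × .625 = 1.75. The documents do not support this. The .80 comes from a pre/post simplification. With T5 as the posttest, every recipient has already received relief and nothing is diluted. If four waves are averaged, precision rises: under compound symmetry (assumed) the residual variance falls from 1 − .68² = .538 to (1 + 3 × .68)/4 − .68² = .298. The noncentrality is then 2.80 × .625/√(.298/.538) = 2.35 and power about .65. The loss depends on the waves used. The protocol also says that power for this aim cannot be assessed in advance.

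**Size and status.** The shock inputs have no source in the protocol, and the apparent harm of +0.08 to +0.09 is below the smallest effect considered for this aim (.19). Aim c is secondary and its estimates are called preliminary. Both points stand and limit the weight of the finding.

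**Conclusion.** The point holds in this form: a baseline-only score is a poor rule for an exposure that can begin at any time over 32 months, when the protocol itself expects later shocks to move the outcomes. The direction of bias, toward no benefit or apparent harm, rests on one plausible inference: that people hit by such shocks are more likely to obtain relief.

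The size is illustrative only. In the central scenario (10% per interval, 0.5 SD, log-odds 1), a true -0.23 appears as -0.14 with wave-level receipt and -0.06 with an ever-received label. The shrinkage of 0.23 to 0.14, range 0.06 to 0.23, applies only if that label is used and depends on when receipt occurs. No figure for lost power is claimed. This should be changed, but no primary aim depends on it.

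**What to change.** Rewrite Secondary Aims (c) so that receipt is time-varying:

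1. Record at each wave whether relief was received and when, and date unemployment and COVID infection relative to receipt.
2. At each wave, match new recipients to people who have not yet received relief. Use the preceding wave's covariates and outcomes, plus shocks reported since that wave that occurred before receipt. Leave out changes after receipt, since relief may have caused them.
3. Count only waves after receipt as exposed.
4. State that need not captured by the surveys may still confound the result.

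The cost is analysis wording, more programming, smaller matched sets and wider intervals. No extra survey waves are needed, but the timing of receipt and of shocks must be in the questionnaire. If it is not recorded, the order of events within an 8-month interval cannot be recovered, and the estimate should be reported with that limitation.
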